### Statistical analyses

#### Basic analyses

The sample and its characteristics will be analysed employing descriptive statistical methods. Means, standard deviations and other basic statistics for all relevant variables will be calculated for descriptive purposes. Between-group comparisons at baseline will be performed to test randomization and assess differences between treatment and control groups, as well as between participants at different study locations. The internal reliabilities of the instruments used will be analysed employing Cronbach’s α. For all statistical tests, significance levels will be set at α = 0.05, with the Holm-Bonferroni method used to control family-wise error rates, where appropriate. Multiple imputation will be employed in the case of dropouts or other missing data. Intention-to-treat analyses will be carried out, so that all participants who are randomized into either group will be included in final analyses.

#### Effect evaluation

The main effect of NET as compared to TAU and the waiting list control condition on the primary outcomes of PTSD symptom severity, depressive symptoms, psychological distress, resilience and cognitive performance will be analysed employing analyses of covariance. Potential confounding factors (age, gender, treating unit) will be included as covariates. The main effects of NET as compared to TAU and the waiting list condition on the secondary outcomes of trauma memory quality and trauma-related cognitions will be similarly analysed employing analyses of covariance. For all analyses of covariance, effect sizes will be reported as partial η^2^, with 95 % confidence intervals included.

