There are two control conditions. First, the time each child spends waiting for treatment to begin, typically three months, will be considered a waiting list control condition. Second, each participant will be randomized into one of two groups. One group will receive NET, acting as the study group, and the other group, receiving TAU, will act as a positive-control group. The trial is parallel-group in nature, with a randomized block design with varying block sizes and an allocation ratio of 1:1.

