### Procedure

A sequential procedure will be applied to data collection. Whenever a child is identified as a potential participant by a clinician at one of the co-operating units, information concerning the intervention and the related research is provided both to the participant him/herself and to his/her parents. If they are willing to participate in the research, informed consent will be requested from the child and his/her parents.

Waiting list control baseline data (T0) will be collected during this first meeting with the clinician. The children will then be randomly assigned to EITHER the ‘treatment as usual’ group (n = 40) OR the ‘NET intervention’ group (n = 40). Because of the treatment queues currently present at most of the treatment units, all participants will first be placed under waiting-list conditions for approximately three months (waiting list control condition, n = 80). In the unlikely case that there is no treatment queue at the moment, the participant will begin NET or TAU immediately and will not contribute waiting list control data.

At the start of the intervention or TAU, pre-test (T1) data will be collected from all participants. The T1 data will serve as an end measurement for the waiting list control condition and as the pre-test measurement for the NET intervention and the TAU control condition.

Data (T2) will also be collected once during the treatment for both the NET and the TAU groups. This will allow for proper analysis of mediating mechanisms. In the NET group, this assessment will take place at the time when the worst traumatic memories have been narrated.

Post-test data (T3) will be collected from participants in both groups, immediately after the intervention for the NET group, and after three months of treatment for the TAU group, and follow-up data (T4) will be collected during a joint family meeting, three months later.

In most cases, the clinician working as the therapist will also act as the assessor and collect data from the patients he/she is treating. In some cases, members of the research team may carry out some assessments, particularly for follow-up. Interpreters are used whenever needed during assessments, and will be present during all assessment and treatment sessions for children who are not fluent in Finnish.

The procedure will be continued until the sample size reaches the goal of n = 80, with data collection estimated to finish during 2017.

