### Sample size calculation

The sample size was calculated using G*Power 3.1.9.2 [65]. Earlier results obtained on NET with children [5, 31] suggest large between-groups effect sizes of *d =* 0.7–1.0 for PTSD symptom severity for NET vs. waiting list. For determining the effectiveness of NET vs. waiting list, with α = 0.05, *d =* 0.85 (*f ≈ 0.40)* and a priori test power = 0.80 (β = 0.20), 52 participants would be required for analyses of covariance of fixed effects, main effects and interactions on primary outcomes.

There are no effect size estimations available for TAU as offered to traumatized children at participating clinics, nor could such estimations be reliably made, taking into account the diverse nature of TAU expected. However, at least some effectiveness for TAU over a waiting list can be assumed. Thus, in order to tease out differences in NET vs. TAU between-treatments comparisons, we needed to aim for a sample size that is somewhat larger than that required for detecting NET vs. waiting list between-groups differences. At the same time, dropout rates for participation in NET reported in earlier studies are generally very low [29, 66], so little attrition is expected. In light of these considerations and practical limitations, we aim for a sample of 80 participants.

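### NET versus waiting list is a within-child, before-after contrast, but the plan presents and sizes it as a parallel-group randomised comparison and names no within-child term in its ANCOVA

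*Protocol article*

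**What the plan says.** The protocol article has two controls. Trial design defines the first: "the time each child spends waiting for treatment to begin, typically three months, will be considered a waiting list control condition". The second is TAU, to which children are randomised 1:1 against NET. Procedure gives 40 children per arm and 80 for the waiting-list condition, which is all participants. It adds that a child who meets no queue contributes no waiting data. It also fixes the double role of T1: "The T1 data will serve as an end measurement for the waiting list control condition and as the pre-test measurement for the NET intervention".

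Current trial and the opening of Trial design name the waiting list beside TAU as a comparator of a parallel-group randomised trial. The Abstract and Research questions and hypotheses put both comparators into the main hypothesis.

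Sample size calculation sizes only NET versus waiting list. It cites earlier results that "suggest large between-groups effect sizes", takes d = 0.85 (f ≈ 0.40) with 80% power, and concludes that "52 participants would be required for analyses of covariance of fixed effects, main effects and interactions on primary outcomes". The target of 80 is then described as "somewhat larger than that required for detecting NET vs. waiting list between-groups differences".

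Effect evaluation covers "The main effect of NET as compared to TAU and the waiting list control condition on the primary outcomes" by analyses of covariance adjusted for age, gender and treating unit. It names no child effect, pairing or repeated-measures term. Basic analyses states that "significance levels will be set at α = 0.05".

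**The concern.** Two things follow from the way the waiting list is built.

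First, the two sides are correlated. Up to 40 children appear in both, and T1 is used twice. An ANCOVA that treats the rows as separate children gives a standard error that does not match the sampling variance of the contrast.

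Second, nobody is randomised to wait and waiting always comes first. Natural recovery, regression to the mean and repeat testing therefore differ between the two periods for reasons unrelated to NET. Background itself says that most survivors recover with time, and also that symptoms persist for years in some.

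The contrast carries weight. It is half of the main hypothesis, it is the only comparison with a formal sample size, and Risks and limitations relies on it to offset the variety of TAU. That section does not list its sequential, non-randomised nature as a limitation. As described, a before-after result could be read as a result of the randomised trial.

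**Working it through.** **Reproducing the 52.** Inputs from Sample size calculation: α = 0.05, power 0.80, f = 0.40. For a fixed-effects ANCOVA with two independent groups, the noncentrality is λ = N f², with 1 and N − 2 degrees of freedom (fewer with covariates). At N = 52, λ = 52 × 0.16 = 8.32 and power is 0.807. Then 52 is the smallest adequate N, and this also holds with one or three covariates. The unrounded f = d/2 = 0.425 would give 46. So the stated figure is that of an independent two-group model with f rounded down.

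**Variance of the contrast.** Take unit variance at each visit, n₁ = 40 NET children, n₂ waits, 40 children in both, and r = the correlation between a child's two contributions.

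- Independent groups: V₀ = 1/n₁ + 1/n₂
- Actual design: V = V₀ − 2r × 40/(n₁n₂)
- True over reported SE: k = √(V/V₀)
- True type I error of a nominal 5% test: 2[1 − Φ(1.96/k)]

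Let ρ be the correlation between visits. Then r is:

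- Change scores: −0.5 under compound symmetry (CS); −(1 − ρ)/2 under a first-order autoregressive pattern (AR1)
- End scores, T3 against T1: ρ
- End scores adjusted for each period's starting score: −ρ²/(1 + ρ) under CS; 0 under AR1

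Worked cases for 40 against 80, where V₀ = 0.0375 per unit variance:

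- Change scores under CS have variance 2(1 − ρ). So V₀ = 0.075(1 − ρ), V = 0.100(1 − ρ) and k = √(0.100/0.075) = 1.155.
- End scores have V = 0.0375 − 0.025ρ. At ρ = 0.6, k = √(0.0225/0.0375) = 0.775.

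The documents give no ρ, so each entry runs from ρ = 0.4 to ρ = 0.8.

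| Outcome form | 40 NET v 80 waits: k; type I error | 40 NET v own 40 waits: k; type I error |
|---|---|---|
| Change, CS | 1.155; 9.0% | 1.225; 11.0% |
| Change, AR1 | 1.095 to 1.033; 7.4% to 5.8% | 1.140 to 1.049; 8.6% to 6.2% |
| End score, listed covariates only | 0.856 to 0.683; 2.2% to 0.4% | 0.775 to 0.447; 1.1% to below 0.1% |
| End score plus starting score, CS | 1.037 to 1.112; 5.9% to 7.8% | 1.056 to 1.164; 6.3% to 9.2% |
| End score plus starting score, AR1 | 1.000; 5.0% | 1.000; 5.0% |

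Simulation (8,000 trials per setting, 40 against 80, ρ = 0.5 and 0.7) agrees: change under CS 8.4% and 9.2%; end scores under CS 1.7% and 0.8%; starting score added 6.0% and 6.7% under CS, 5.4% and 5.1% under AR1. A separate simulation over ρ = 0.4–0.8 put the start-adjusted form at about 4–8%.

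**What a correct standard error does not cure.** Analyse 40 NET children as pairs on (T3 − T1) − (T1 − T0), whose SD under CS is √[6(1 − ρ)]: 1.73 at ρ = 0.5 and 1.34 at ρ = 0.7. A difference between the periods of 0.3 SD that has nothing to do with treatment is then significant in 19% to 28% of trials, and one of 0.5 SD in 43% to 63%.

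**The case against.** The strongest reply is that independence is inferred. Effect evaluation says only that ANCOVA is used. It does not name the outcome form, say whether the starting score is a covariate, or rule out a repeated-measures version, and an article may leave such detail to an analysis plan. The evidence for independent groups comes from the sample size section, which shows how N was found rather than how the data will be modelled. This stands in part: the size and direction of any standard-error fault cannot be fixed from the text. It does not excuse the structure that the text does state, namely a between-groups sizing and a parallel-group randomised label for a contrast within the same children.

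Several stronger readings are tempting and not supported.

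- *The error bars are certainly wrong, and too small.* They may be too small, too large or about right, as the table shows.
- *The trial is too small for this contrast.* At d = 0.85 on the difference between the two changes (CS, 80% power), a paired analysis needs 42, 35, 29, 22 and 16 children at ρ = 0.4, 0.5, 0.6, 0.7 and 0.8. Forty NET children with waiting data suffice except near 0.4.
- *The time confounding favours NET.* Steady recovery favours NET on end scores, because T3 is later than T1. Recovery that slows, or regression to the mean after referral, falls mainly in the waiting period and works against NET on change scores.
- *The same children supply both sides entirely.* About half of the 80 waits come from TAU children.
- *The design is hidden.* Trial design and Procedure disclose it, the hypotheses never call the waiting list randomised, and Conclusions does not mention it.
- *The randomised comparison is damaged.* NET versus TAU does not use the waiting-list contrast.

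**Conclusion.** The concern holds in this form: NET versus waiting list is a non-randomised, within-child, fixed-order contrast, and the protocol frames and sizes it as a parallel between-groups comparison while its analysis section addresses neither the overlap nor the order. If the overlap is ignored, the true error of a nominal 5% test lies anywhere from well below 5% (end scores) to about 11% (change scores), and is near 5% in the start-adjusted autoregressive case. These figures rest on assumed correlations of 0.4–0.8, equal variances, no dropout and every child having waited. The confounding with time needs no assumed correlation, but its direction and size are unknown. This is more than missing detail, because the document misdescribes one of its two main comparisons. It does not touch NET versus TAU.

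**What to change.** In Effect evaluation, separate the two comparisons. Keep NET versus TAU as the only randomised comparison; its analysis need not change on this account. Analyse NET versus waiting list as a within-child contrast: either paired, or by a repeated-measures or mixed model with child-level covariance. Enter visit as a categorical factor. A fitted linear waiting slope would make the NET effect depend on extrapolating that slope into the treatment period.

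In the Abstract, Current trial, Research questions and hypotheses, Trial design and Sample size calculation, label NET versus waiting list as a supportive, non-randomised before-after comparison, open to natural recovery, regression to the mean and repeat testing. State in Sample size calculation that 52 assumes independent groups.

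One limit should be stated with the change. Table 1 schedules the cognitive tests only at T0 and T4, so that outcome has no end-of-wait value and cannot enter this contrast.

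The cost is wording and model specification, with no new data. The waiting-list claim becomes weaker.

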In this paper, we describe a randomized controlled trial (RCT) evaluating the effectiveness and potential mechanisms of change of a targeted intervention, Narrative Exposure Therapy, NET [14], for children who suffer from posttraumatic stress symptoms due to experiences of war or armed conflict. To our knowledge, it is the first effectiveness study of NET as implemented in the context of the existing healthcare system of a high-income country. In this context, it is also the first trial to explore whether changes in the quality of traumatic memories and posttraumatic cognitions are potential candidates for effective mechanisms of change in PTSD symptom reduction among war-affected children in treatment. This study protocol aims to present all relevant information pertaining to this randomized controlled trial, as set out by the CONSORT 2010 guidelines [15].

For traumatized children in general, cognitive-behavioral therapy (CBT) has been repeatedly found to be effective in reducing PTSD and other symptoms [16–18], and trauma-focused cognitive-behavioral therapy (TF-CBT) is recommended as the primary treatment for PTSD for both adults and children in several countries [19,20]. For children affected by war specifically, a variety of group and individual interventions have been implemented and studied all over the world. Reviews have reported evidence on the effectiveness of such psychosocial interventions in alleviating PTSD, depression and anxiety symptoms in children affected by armed conflict [21–23]. However, reductions in symptoms have often been modest, and study designs have lacked rigor, with only a small minority representing RCTs.

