
## Methods/Design

### Trial design

We are conducting a multicenter, parallel-group, randomized, controlled trial comparing NET to a waiting list condition and TAU at several treatment units located in Finland. Five sets of assessments will be carried out: baseline, T0 (3 months before the start of treatment); pre-test, T1 (when treatment begins); during treatment, T2 (approximately halfway through the treatment); post-test, T3; and follow-up, T4 (three months after treatment). A three-month follow-up period is considered long enough to assess medium-term maintenance of treatment gains, but still short enough to be practically implementable in this context, where drop-outs due to, e.g., asylum seekers being denied asylum and leaving the country, are possible. A three-month follow-up period also means that the T0, T1, T3 and T4 measurements are conducted at equal intervals of three months. Table 1 presents the measurements taken at each point of assessment.

**Table 1 Tab1:** Points of assessment and measures used

T0 Baseline	T1 Pre-test	T2 Midpoint	T3 Post-test	T4 Follow-up
Approx. three months before start of treatment	At start of treatment	Approx. halfway through treatment	Immediately after treatment	Three months after treatment
– CRIES	– CRIES	– CRIES	– CRIES	– CRIES
– DSRS	– DSRS	– C-PTCI	– DSRS	– DSRS
– SDQ	– SDQ	– TMQQ	– SDQ	– SDQ
– C-PTCI	– C-PTCI	– SUDS (each session)	– C-PTCI	– C-PTCI
– CYRM	– CYRM		– TMQQ	– TMQQ
– TMQQ	– TMQQ		– CYRM	– CYRM
– PDEQ			– CSRS	– CSRS
For subsample:				For subsample:
– WMTB-C				– WMTB-C
– RPM				– RPM
– TMT				– TMT

*C-PTCI*, Children’s Post-Traumatic Cognitions Inventory; *CRIES*, Children’s Revised Impact of Event Scale; *CSRS*, Child Session Rating Scale; *CYRM*, Child and Youth Resilience Measure; *DSRS*, Depression Self-Rating Scale for Children; *PDEQ*, Peritraumatic Dissociative Experiences Questionnaire; *RPM*, Raven’s Progressive Matrices; *SDQ*, Strengths and Difficulties Questionnaire; *SUDS*, Subjective Units of Distress Scale; *TMT*, Trail Making Test; *TMQQ*, Trauma Memory Quality Questionnaire; *WMTB-C*, Working Memory Test Battery for Children

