### Measures

#### Primary outcomes

*Posttraumatic stress symptoms* will be measured at T0, T1, T2, T3, and T4, employing the children’s version of the Revised Impact of Event Scale (CRIES) [49]. CRIES consists of 13 items covering the re-experiencing, avoidance and hyperarousal symptom dimensions. Children estimate the occurrence of each symptom on a 4-point scale. CRIES-R has been found to have good reliability among war-affected children [50].

*Depressive symptoms* will be measured at T0, T1, T3, and T4 employing the Depression Self-Rating Scale for Children (DSRS) [51]. The measure includes 18 items that assess the cognitive, affective, and behavioral dimensions of depression. At each item, children estimate on a 3-point scale whether they have experienced the symptom over the preceding two weeks.

*Psychological distress* will be measured at T0, T1, T3, and T4 employing the Strengths and Difficulties Questionnaire (SDQ) [52]. One form is provided for self-assessment by the child and another for a parent or guardian, if available. The measure covers emotional and behavioral problems and hyperactivity. Each dimension consists of 5 items evaluated on a 3-point scale as to how well the description fits the situation of the child.

*Resilience* will be measured at T0, T1, T3, and T4 using an adapted, focus-group-based version of the Child and Youth Resilience Measure (CYRM) (28-item version originally developed by Ungar and Liebenberg [53], and validated in [54]). CYRM is a questionnaire exploring the individual, relational, communal and cultural resources that may bolster the resilience of 9–23-year-old youth. The participant reports on a 5-point scale as to what extent he/she feels he/she has certain resources.

*Cognitive performance (of a subset of participants)* will be addressed by measuring a) attention and working memory, b) non-verbal, general cognitive performance and c) executive functioning. Attention and working memory will be measured at T0 and T4 employing performance-based sub-tests for verbal and spatial working memory from the Working Memory Test Battery for Children (WMTB-C) [55]. Non-verbal, general cognitive performance will be assessed at T0 and T4 employing age-appropriate versions of Raven’s Progressive Matrices (RPM) [56]. Executive functioning will be measured at T0 and T4 employing the Trail Making Test (TMT) [57].

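### For NET versus TAU, neither T3 nor T4 is named as the visit of the primary test on the four repeated primary outcomes, Holm's family leaves visits open, and no analysis addresses maintenance

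*Protocol article*

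**What the plan says.** The only description of the effect analysis is in Effect evaluation: analyses of covariance of "The main effect of NET as compared to TAU and the waiting list control condition on the primary outcomes". On adjustment it says "Potential confounding factors (age, gender, treating unit) will be included as covariates". It gives no visit, no time factor and no baseline score.

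Under Primary outcomes, the depression scale "will be measured at T0, T1, T3, and T4 employing the Depression Self-Rating Scale for Children". SDQ and CYRM have the same four visits, and CRIES has these plus T2. Cognitive performance is measured at T0 and T4 only, in a subsample of 20 (Procedure).

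Table 1 labels T3 as post-test and T4 as follow-up. On the purpose of T4, Trial design says "A three-month follow-up period is considered long enough to assess medium-term maintenance of treatment gains".

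Under Research questions and hypotheses, the first hypothesis, on the primary outcomes, states no time. The second, on trauma-related memory and cognitions, is tied to the end of treatment.

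Basic analyses sets α = 0.05 for all statistical tests and uses Holm-Bonferroni where appropriate, without defining the family.

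**The concern.** The time of assessment is part of what a primary outcome is. With T3 and T4 both available and neither named, the claim that NET outperforms TAU on a symptom scale could rest on either visit. If it may rest on whichever is more favourable, and multiplicity is counted by outcome only, the error rate exceeds the stated 0.05.

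The visits also answer different questions. T3 is taken three months into TAU even where TAU continues (Control intervention), and T4 follows three months later. By T4 the NET course has ended, while some TAU children may have had further treatment. Choosing the visit therefore changes the treatment contrast as well as the number of tests.

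T4 is collected to show whether gains last, yet nothing under Statistical analyses examines change from T3 to T4.

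Timing adds weight. Ethical issues schedules a NET-TAU comparison once all measurements are in for the first 20 participants. A visit chosen after that would be chosen after results from both visits had been seen.

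**Working it through.** **Inputs from the protocol.** α = 0.05; five primary outcomes, four of them at T3 and T4 and one at T4 only; target N = 80, allocated 1:1; required N of 52 for NET versus waiting list at f ≈ 0.40 and power 0.80.

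**Inputs assumed.** Tests are two-sided. The T3-T4 correlation of the test statistics, ρv, is 0.5 to 0.9. The between-outcome correlation, ρo, is 0.3 to 0.7. The T4-only cognitive outcome is independent of the others and counts as one test, and SDQ counts as one test.

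**Step 1, the plan's own figure.** For an F test with 1 numerator degree of freedom, two groups, one covariate and noncentrality λ = N f²: at N = 52, λ = 52 × 0.16 = 8.32 and power is 0.807; at N = 51, power is 0.799. The stated 52 reproduces. It is sized for one test at 0.05 and is not in dispute.

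**Step 2, one outcome tested at 0.05 at both visits.** Error = 1 − P(|Z₃| < 1.96 and |Z₄| < 1.96). With independent visits this is 1 − 0.95² = 0.0975. With bivariate normal statistics it is 0.091 at ρv = 0.5, 0.084 at 0.7 and 0.070 at 0.9.

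**Step 3, the family of five outcomes.** Under no NET-TAU difference, Holm makes at least one false rejection exactly when the smallest p-value is at or below 0.05/m. With five outcomes, m = 5 and the first threshold is 0.05/5 = 0.010. With every outcome-by-visit test counted, m = 4 × 2 + 1 = 9 and the threshold is 0.05/9 = 0.0056. Family-wise error from 1,000,000 simulated sets per row:

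| ρv | ρo | One fixed visit, m = 5 | Better of T3 and T4, m = 5 | Both visits, m = 9 |
|---|---|---|---|---|
| 0.5 | 0.3 | 0.048 | 0.080 | 0.046 |
| 0.5 | 0.5 | 0.045 | 0.075 | 0.043 |
| 0.5 | 0.7 | 0.040 | 0.065 | 0.038 |
| 0.7 | 0.3 | 0.048 | 0.075 | 0.043 |
| 0.7 | 0.5 | 0.045 | 0.070 | 0.040 |
| 0.7 | 0.7 | 0.040 | 0.061 | 0.036 |
| 0.9 | 0.3 | 0.048 | 0.065 | 0.038 |
| 0.9 | 0.5 | 0.045 | 0.061 | 0.035 |
| 0.9 | 0.7 | 0.040 | 0.053 | 0.031 |

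**Step 4, the price of counting visits.** At N = 80, same F test: with d = 0.85 (the plan's value for NET versus waiting list), power at the first Holm threshold falls from 0.874 (α = 0.010) to 0.825 (α = 0.0056). With d = 0.5, assumed for NET versus TAU because the protocol gives no effect size there, it falls from 0.349 to 0.277.

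**Step 5, the waiting-list comparison.** The waiting condition is a single interval of about three months that ends at T1 (Procedure). Counted from T1, T3 is about three months on and T4 about six. Only T1-to-T3 matches the waiting interval in length, and the text does not say that this is the window used.

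**The case against.** The strongest reply is that Holm may already cover the problem. Basic analyses speaks of all statistical tests, and counting T3 and T4 tests in the family fits that wording at least as well as counting outcomes alone. On that reading the error is controlled (0.031 to 0.046 in the table). A reader might infer that the plan does inflate its error rate, or that success at either visit is enough. The protocol says neither; the inflation is conditional.

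A second reply is that the visit labels, and the maintenance purpose given to T4, point to T3 as the main visit. They do, but they do not fix it, and cognition has no T3 measurement.

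Third, a reader might infer that the plan commits to separate analyses at each visit with no arm-by-visit term. The text does not say separate, and a repeated-measures analysis of covariance is not excluded. The sample-size section mentions interactions, though that may only be the software's name for the procedure. The model is unstated rather than wrongly stated.

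Fourth, it is tempting to say that every hypothesis gets two chances. That fails for cognitive performance (T4 only), for the memory and cognitions hypothesis (end of treatment), and largely for the waiting list, whose natural counterpart is T1 to T3.

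Finally, model form is commonly left to an analysis plan. That stands for the choice of model. It does not stand for the visit: Effect evaluation already fixes method, covariates and effect-size measure, and the Background says "This study protocol aims to present all relevant information pertaining to this randomized controlled trial".

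**Conclusion.** The point holds for NET versus TAU on CRIES, DSRS, SDQ and CYRM. The protocol does not name the visit of the primary test, does not say whether visits belong to the Holm family, and states no analysis of maintenance.

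The cost in error rate depends on the reading. With Holm over five outcomes and a free choice of visit, family-wise error is about 0.05 to 0.08 instead of 0.04 to 0.05. With all nine tests in the family there is no inflation, but the first threshold is nearly halved. The figures rest on assumed correlations and on one test each for SDQ and cognition. The protocol lists child and parent SDQ forms and several cognitive tests, so the real number of tests may be larger. This should be settled before NET-TAU results are examined, but it does not undermine the design or the sample-size figure.

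**What to change.** - For NET versus TAU, name the T3 contrast as the single primary test for CRIES, DSRS, SDQ and CYRM, and the T4 contrast for cognitive performance. Apply Holm over those tests.
- Adjust each test for the outcome's own baseline score and state which baseline is used. T0 precedes randomization, whereas Procedure treats T1 as the pre-test for both arms, so the choice needs a sentence of justification.
- Report the T4 contrast and the difference between arms in T3-to-T4 change as secondary, from a repeated-measures model with arm, visit and arm-by-visit, or from an equivalent analysis of covariance. This gives the maintenance question an analysis.
- For the waiting-list comparison, set T1-to-T3 against the T0-to-T1 waiting interval and do not use T4.

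The cost is wording and slightly more modelling, with no new data. The downside is that an effect seen only at T4 becomes a secondary result.

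### The ANCOVA covariate list omits the pre-randomisation (T0) score of the outcome, which costs precision in the randomised NET versus TAU comparison

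*Protocol article*

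**What the plan says.** Under Effect evaluation, the protocol article states that PTSD severity, depressive symptoms, distress, "resilience and cognitive performance will be analysed employing analyses of covariance". The next sentence gives the adjustment set: "Potential confounding factors (age, gender, treating unit) will be included as covariates". Trauma memory quality and trauma-related cognitions are to be handled in the same way. The section states neither the dependent variable (post-treatment score or change) nor the time point.

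Pre-treatment scores are available. CRIES "will be measured at T0, T1, T2, T3, and T4, employing the children’s version of the Revised Impact of Event Scale". Table 1 shows DSRS, SDQ, CYRM, TMQQ and C-PTCI at both T0 and T1 as well. The cognitive tests have one pre-treatment score only: "Attention and working memory will be measured at T0 and T4", and the same holds for the other two tests, in a subsample of 20.

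Under Procedure, T0 is collected at the first meeting, before random assignment. T1 comes after the wait and has two roles: "The T1 data will serve as an end measurement for the waiting list control condition and as the pre-test measurement for the NET intervention" and for TAU. The only use of baseline described under Basic analyses is a comparison of groups to check the randomisation.

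**The concern.** In a trial with repeated measurement of the same scale, the baseline score of the outcome is usually the most informative covariate. A named list of three covariates that leaves it out invites an analyst to fit a model without it.

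Two things would be at stake. First, stable differences in severity between children stay in the error term. Entry requires symptoms judged significant but sets no scale cut-off and no formal diagnosis (Inclusion and exclusion criteria), so those differences may be wide. Second, a chance difference in baseline severity between the arms passes into the estimate. Comparing the groups at baseline would reveal such a difference but would not correct it.

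This matters most for NET versus TAU. The Sample size calculation section says that no effect-size estimate exists for TAU, assumes that TAU has some effect of its own, and settles on 80 children partly for practical reasons.

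**Working it through.** **Inputs from the protocol article.** N = 80, allocated 1:1 (40 per arm). Alpha: "For all statistical tests, significance levels will be set at α = 0.05". Power 0.80. Planning effect for NET versus waiting list d = 0.85, entered as f of about 0.40, giving 52 participants.

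**Inputs assumed.** The correlation r between the T0 score and the outcome is not in the protocol; 0.3 to 0.7 is used. A NET versus TAU difference of 0.5 SD is illustrative only.

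**Step 1: the plan's own figure.** For two groups and numerator df 1, the noncentrality is λ = N·f². With f = 0.40 and N = 52, λ = 52 × 0.16 = 8.32 and power is 0.807, so 52 reproduces. It does so with no reduction in variance from any covariate. (Exact conversion, f = 0.85/2 = 0.425, would give 46, so 52 rests on the rounded f.)

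**Step 2: effect of adding T0.** Adjustment multiplies the residual variance by (1 − r²). Then f = d / (2√(1 − r²)) and λ = N·d² / (4(1 − r²)). The detectable difference is about 0.634 × √(1 − r²), and the equivalent sample size is 80 / (1 − r²).

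| T0 in model | 1 − r² | Detectable d, 80% power | λ at d = 0.5 | Power at d = 0.5 | Equivalent N |
|---|---|---|---|---|---|
| No | 1 | 0.634 | 5.00 | 0.598 | 80 |
| Yes, r = 0.3 | 0.91 | 0.605 | 5.49 | 0.639 | 88 |
| Yes, r = 0.5 | 0.75 | 0.549 | 6.67 | 0.722 | 107 |
| Yes, r = 0.7 | 0.51 | 0.453 | 9.80 | 0.871 | 157 |

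**Step 3: cost in degrees of freedom.** With seven df already spent on other covariates, the detectable difference without T0 moves only from 0.634 to 0.635. One more df is immaterial at N = 80. In the cognitive subsample, if all five named units contribute, the residual df are 20 − 2 (arms) − 1 (age) − 1 (gender) − 4 (units) = 12, and T0 would leave 11.

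**Step 4: chance imbalance.** With 40 per arm, the baseline difference has standard error √(2/40) = 0.22 SD, so about 1 trial in 20 has a difference beyond 1.96 × 0.22 = 0.44 SD in either direction. A 0.44 SD imbalance shifts an estimate not adjusted for baseline by r × 0.44: 0.13 SD at r = 0.3 and 0.31 SD at r = 0.7.

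**Step 5: which pre-treatment score.** T0 precedes random assignment. T1 follows it: "At the start of the intervention or TAU, pre-test (T1) data will be collected from all participants". The Randomization section says that clinicians, who mostly act as assessors, are not blinded after T0. T1 is therefore a post-randomisation measurement usually taken by someone who knows the arm. It is also the end point of the waiting period, so it cannot be a covariate in the waiting-list contrast.

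**The case against.** The strongest reply is that the article does not exclude the baseline score. It lists confounders without calling them the only model terms, the label ANCOVA often implies a baseline covariate, T1 is called a pre-test, and some hypotheses are worded as reductions. A reader might infer from the list that raw post-treatment scores will be compared. The text does not support that: three covariates are named and the dependent variable is not stated. This part of the reply stands. But no sentence gives a pre-treatment score a place in the effect model or defines a change score, while a covariate list is given. If baseline adjustment was intended, the same sentence still needs correcting. If change scores were intended, their relative variance 2(1 − r) is 1.4, 1.0 and 0.6 at r = 0.3, 0.5 and 0.7, against 0.91, 0.75 and 0.51 for adjustment.

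A second reply is that randomisation protects the comparison. That stands for bias: a reader might infer that the NET versus TAU estimate is biased, and in expectation it is not.

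A third is that the gain may be modest. This also stands. T0 lies about six months before T3 and nine before T4, with treatment in between, so r may be low; at r = 0.3 the detectable difference falls only from 0.63 to 0.61 SD. Treating unit covers inpatient wards and outpatient clinics and may already absorb some severity, so the r that counts is the partial correlation given age, gender and unit.

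**Conclusion.** The point holds as a loss of precision in the randomised NET versus TAU comparison, with chance imbalance in baseline severity left uncorrected. It is not a source of bias or of an inflated error rate. On the assumed r of 0.3 to 0.7, naming T0 as a covariate would lower the detectable difference from about 0.63 SD to 0.61–0.45 SD and raise power at 0.5 SD from about 0.60 to 0.64–0.87. These gains are somewhat smaller if the three listed covariates already explain part of the variance. They rest on a correlation and an effect size that the protocol does not supply.

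A reader might also infer that entry has no symptom requirement, or that any pre-treatment score would serve equally. Neither is supported: significant symptoms are required and only a numeric cut-off is absent, and T1 is taken after allocation.

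**What to change.** Amend the covariate sentence under Effect evaluation to read: *For the NET versus TAU comparison, the T0 score on the same measure, age, gender and treating unit will be included as covariates.* Apply it to every primary and secondary outcome that has a T0 score.

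Describe the waiting-list contrast separately. It is not a comparison of randomised groups, T1 is its outcome and must not be among its covariates, and it needs its own model.

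No new data are needed. The cost is one degree of freedom, negligible at N = 80. In the cognitive subsample of 20 it is not negligible alongside age, gender and unit, so the covariate set for those outcomes should be considered separately. Making the change before outcome data are compared also removes any later discretion over whether baseline is added.
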